### Planning reproducibility

Participants have all subsequent planning and treatment using the chosen BH technique. Four planning computed tomography (CT) scans are acquired for each participant. The scans are acquired sequentially within a 5 min timeframe, with no patient-repositioning between scans, to minimize the impact of repositioning or physiological variation. The Gross Tumor Volume (GTV), tumor surrogates and OARs are contoured on the first planning CT. Post-processing and measurements are completed using a customized workflow in MIM Maestro® software (MIM Software Inc, Cleveland OH). The first planning CT is automatically fused to subsequent CTs. Initially, a bone algorithm fusion corrects any gross patient misalignment. Then, a tumor, surrogate or fiducial marker fusion corrects for tumor/organ position. Contours are automatically generated onto each subsequent CT. Resultant contours are reviewed, and manually edited if required to account for deformation. The inter-BH displacement of the tumor and OARs are measured, with bone fusion as the starting position. Planning R_BH_ of tumour/surrogate and OARs is defined as follows:*R*_*BH*_ Position, in three planes, of the tumor/surrogate or OAR contour centroid and contour surface in CT1 compared to the position in CT2-4, resulting in three observations. The mean of the absolute values of the cumulative sum of each observation will be calculated.

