### Treatment reproducibility

Intra-fraction and inter-fraction R_BH_ is measured for each participant. For all treatment fractions, 3D volumetric Cone Beam Computed Tomography (CBCT) images are acquired using Elekta XVI™ (Elekta, Stockholm, Sweden) before treatment delivery. For participants treated with SABR, post-correction, during, and post-treatment CBCTs are also acquired. Each CBCT is a 360° acquisition using several BHs, with acquisition paused between BHs. The CBCT is automatically fused to the planning CT with a bone algorithm to correct patient setup. Then, a soft-tissue fusion corrects for tumor position. Tumor displacement is measured as the correction applied after accounting for patient setup. Treatment R_BH_ of tumour is defined as follows:*Inter-Fraction R*_*BH*_ Position, in three planes, of the tumor/surrogate on planning CT compared to the position on CBCT1, at each treatment fraction. Results will be collated for all fractions, and averaged.*Intra-Fraction R*_*BH*_ For those participants with multiple CBCTs per fraction, the position, in three planes, of the tumor/surrogate on CBCT1 compared to the position on each subsequent CBCT, at each treatment fraction. The mean values of the absolute value of the cumulative sum of each observation will be calculated.

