To evaluate treatment R_BH_, correlation coefficients will be estimated as fixed-effects, to indicate the consistency between the inter-fraction and intra-fraction observations. The treatment mean R_BH_, will be compared to the pre-planning and planning results, and allow an assessment of the correlation between these paired means. The 95% confidence interval in the paired observations will be compared to a non-inferiority margin of ± 2 mm, with Bland–Altman plots and the Pitman’s test used to test for any indication of bias in the treatment R_BH_ for comparison with pre-planning and planning means. However, it is expected that that the difference between the pre-planning, planning and treatment values may reduce over time, and these differences will be assessed descriptively, and compared to the non-inferiority margin of ± 2 mm.

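### Planning R_BH and inter-fraction R_BH appear to share the first planning CT as reference, which biases their planned correlation upward, so a positive value does not show a stable participant trait

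*Protocol article*

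**What the plan says.** All places are in the protocol article.

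- **Planning reproducibility.** Four CTs are taken in one sitting. Planning R_BH uses the position of the "contour centroid and contour surface in CT1 compared to the position in CT2-4, resulting in three observations". The scale is a magnitude: "The mean of the absolute values of the cumulative sum of each observation will be calculated". The registration is bone-based: "The inter-BH displacement of the tumor and OARs are measured, with bone fusion as the starting position". The same section states that the GTV, "tumor surrogates and OARs are contoured on the first planning CT".
- **Treatment reproducibility.** Inter-fraction R_BH is the position "of the tumor/surrogate on planning CT compared to the position on CBCT1, at each treatment fraction". This too is bone-referenced: "The CBCT is automatically fused to the planning CT with a bone algorithm to correct patient setup". For aggregation, "Results will be collated for all fractions, and averaged". The sentence does not say which of the four planning CTs is meant, and does not mention absolute values.
- **Statistical analysis.** The treatment mean R_BH "will be compared to the pre-planning and planning results, and allow an assessment of the correlation between these paired means". The section also plans 95% confidence intervals against a ±2 mm margin and Bland–Altman plots with Pitman's test. It does not say whether the treatment mean is the inter-fraction or the intra-fraction value.
- **Primary outcome measures.** Planning R_BH is outcome c; inter-fraction and intra-fraction R_BH are outcome d.

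**The concern.** If CT1 caught an atypical hold, CT2-4 all lie far from it, and so does CBCT1 at every fraction. If CT1 was typical, both sets of distances are small. One scan's tumor-to-bone offset therefore moves both measures in the same direction. Averaging over fractions does not remove it, because every fraction is measured from the same scan.

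Zero is then not the value to expect when participants do not differ. A moderate positive coefficient could be taken to mean that participants who hold reproducibly at planning also do so at treatment, when it reflects only how typical one scan was. Only SABR participants have further CBCTs in a fraction, so inter-fraction R_BH is the one treatment measure that every participant has. That makes this the likeliest version of the planning-to-treatment correlation to be reported.

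**Working it through.** The document states no correlation to reproduce. Its only related figure, 14–27 participants, is not affected by this point.

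**Inputs from the document.** Planning R_BH averages three absolute differences from CT1. Inter-fraction R_BH averages differences from the planning CT over fractions.

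**Assumptions.** The planning CT is CT1. Inter-fraction differences are taken as magnitudes. Positions are normal, independent and one-dimensional. Every participant has the same hold SD, set to 1. CBCT position has SD s (1, or 0.7 because each CBCT spans several holds). Each participant has a planning-to-treatment shift with SD b. There are 5 fractions.

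**Formulas.** For zero-mean normal U and V with SDs σU and σV and correlation ρ:

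- Var|U| = σU²(1 − 2/π)
- Cov(|U|,|V|) = (2σUσV/π)[√(1 − ρ²) + ρ·arcsin ρ − 1]

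**Planning R_BH.** Each CTk − CT1 has variance 2, and any two have ρ = 0.5.

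- Variance of one absolute difference: 2(1 − 2/π) = 0.7268
- Covariance of two: (4/π)(0.8660 + 0.2618 − 1) = 0.1628
- Variance of the mean of three: (0.7268 + 2 × 0.1628)/3 = 0.3508, so SD 0.59

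**Inter-fraction R_BH.** Each CBCT1 − CT1 has variance v = 1 + s² + b². Two fractions have ρ = (1 + b²)/v. A planning difference and a fraction difference have ρ = 1/√(2v), because CT1 is common to both.

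**Worked case, s = 1, b = 0.** Here v = 2 and the cross-covariance is again 0.1628. The variance of the 5-fraction mean is (0.7268 + 4 × 0.1628)/5 = 0.2756. So r = 0.1628/√(0.3508 × 0.2756) = 0.52.

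**Same steps for the other cases:**

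| s | b | v | cross-covariance | variance of inter-fraction mean | r |
|---|---|---|---|---|---|
| 1 | 0 | 2.00 | 0.1628 | 0.2756 | 0.52 |
| 0.7 | 0 | 1.49 | 0.1902 | 0.2867 | 0.60 |
| 1 | 1 | 3.00 | 0.1319 | 0.5723 | 0.29 |
| 0.7 | 1 | 2.49 | 0.1452 | 0.6183 | 0.31 |
| 1 | 2 | 6.00 | 0.0925 | 1.5780 | 0.12 |
| 0.7 | 2 | 5.49 | 0.0968 | 1.6736 | 0.13 |

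Simulation gives the same values. At s = 0.7 and b = 0, three-dimensional distances give 0.62 and 25 fractions give 0.66. If participant and daily shifts each have SD 1 to 2 hold SDs, r falls from 0.28 to 0.11.

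**Planning R_BH from CT2-4 pairs only.** These pairs contain neither CT1 nor any CBCT, so under the same assumptions the covariance with inter-fraction R_BH is exactly zero. Any two pairs share one scan with ρ = ±0.5, and the sign drops out on absolute values. The variance is again 0.3508, so precision is unchanged.

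**If the inferences fail.** With CT2 as treatment reference, r is about 0.17. With inter-fraction values averaged with their sign, r is about 0.

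**The case against.** Several counterarguments have force.

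- **CT1 and the absolute scale are inferred.** That is correct. The contours lie on the first scan, and the paired differences, Bland–Altman plots and ±2 mm margin make sense only if both measures are magnitudes. Both readings are likely, but neither is written down.
- **The trial is about pre-planning screening.** Pre-planning R_BH comes from fluoroscopy and shares no image with the planning or treatment measures. Intra-fraction R_BH starts from CBCT1. A reader might infer that all the evidence on carry-through to treatment is compromised; it is not. One planned comparison is.
- **The CT1-based association is partly real.** If CT1 was atypical, displacement from that plan really is larger at treatment. With identical participants, s = 0.7 and no shift, the mean inter-fraction displacement is 0.73 hold SDs in the lowest third of planning R_BH and 1.33 in the highest. So it would be wrong to call the correlation empty. What it does not support is reading it as a lasting difference between participants, and the protocol does not itself state that reading.
- **No test of zero correlation is planned.** This also stands. Such a test at the 5% level would reject far too often (47% at 14 and 76% at 27 participants with s = 1, b = 0), but the protocol promises only an assessment of the correlation. Those rates illustrate the size of the effect and are not an error rate of the plan.
- **A zero shift is the least plausible case.** The four CTs are taken within 5 minutes without repositioning, whereas treatment takes place in other sessions. The upper end of the range should not be taken as the expected value.

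**Conclusion.** The point holds in a limited form. On the natural reading of the definitions, the planning versus inter-fraction correlation carries one scan on both sides and is biased upward when participants do not differ. The expected r at 5 fractions runs from about 0.5–0.6 (no shift) through about 0.3 (participant shift SD of one hold SD) to about 0.1 (two hold SDs). This rests on CT1 being the treatment reference, on magnitudes being averaged, and on independent holds. The document gives no variance components, so the size in this trial is unknown.

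A reader might go further and conclude that the Bland–Altman analysis is distorted too. No calculation supports that, and a shared reference does not by itself create a mean difference.

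**What to change.** State which planning CT is the treatment reference and that inter-fraction R_BH is averaged as an absolute value. For the planning versus inter-fraction correlation, also compute planning R_BH from CT2–CT3, CT2–CT4 and CT3–CT4. Base any statement that participant reproducibility carries through to treatment on that version. Keep the CT1-based value for outcome c and for describing displacement from the plan.

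The cost is small. No further imaging is needed, and precision under independent holds is the same. Centroid pairs follow by subtracting signed displacements already recorded. Contour-surface pairs may need one more comparison in the software, because surface distances need not subtract. The CT2-4 version also drops the information on whether CT1 itself was atypical, which is why both versions should be reported.

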## Discussion

A process to compare and select the optimal BH technique for each individual patient, using ABC, was developed. This screening process may be able to select the best BH technique for an individual, which may lead to improved R_BH_. The screening process is being piloted as a prospective clinical trial. The results of this study will be disseminated through publication in peer-reviewed journal(s) and/or conference presentations.

## Data Availability

Not applicable.

## Abbreviations

ABC: Active Breathing Coordinator
BH: Breath-hold
CBCT: Cone-beam computed tomography
CT: Computed tomography
DIBH: Deep-inspiration breath-hold
EBH: Expiration breath-hold
GTV: Gross tumour volume
IBH: Inspiration breath-hold
kV: Kilovoltage
OAR: Organ at risk
RT: Radiation therapy
R_BH_: Reproducibility of breath-hold
RO: Radiation oncologist
SABR: Stereotactic ablative radiotherapy
S_BH_: Stability of breath-hold
T_BH_: Time of breath-hold
UA: Upper abdominal
